### Secondary Outcomes

In this study, the AQoL measures general functioning and quality of life [71], and depression/anxiety/stress symptomatology is measured by the DASS [62]. Hazardous alcohol use is measured by the AUDIT [63], and AUD criteria are measured by the CIDI-alcohol [69]. Engagement will be measured by a process analysis using website visit data.

### Data Analysis

As mentioned prior, the DEAL Project is based on the SHADE resource. Data from the SHADE trials indicate the program is associated with a 1.53 effect size change for depression and 0.86 for alcohol between baseline and 12-month follow-up assessments. However, given the SHADE intervention is therapist-guided and longer than that of the DEAL Project, we anticipate smaller effect sizes. Therefore, in line with other brief Internet-based alcohol multi-session modularized interventions with effect sizes of 0.56 [33], a more conservative medium effect size of 0.50 was used. These effects sizes were entered into GPower 3.1 [74] in order to estimate the sample sizes required to detect similar differences between the treatment and control conditions in the current study. Power was set at 80% and conservative 2-tailed tests were assumed even though a directional hypothesis is proposed. Based on this testing, a sample size of 64 per group was needed (total N=128). A conservative dropout rate is 35% of participants at follow-up. As such, we will aim to recruit 200 participants to the study. This will ensure that we will have sufficient power to conduct the analysis.

The authors, using available software packages, will carry out data coding and analysis. Data on screening, refusals, and dropout are coded and reported as per Consolidated Standards of Reporting Trials (CONSORT) [75], and primary analyses use intention-to-treat. Preliminary analyses check for any baseline or health service utilization differences that may confound with condition effects; later analyses control for these as necessary. Categorical and continuous measures of outcome will be examined using mixed or marginal longitudinal models (ie, mixed model repeated measures, generalized estimating equation modelling) as appropriate. These approaches enable the inclusion of participants with missing data, without using inferior techniques such as last observation carried forward, when data is missing at random [76]. A “completers” analysis on all participants completing at least 75% of the modules will be undertaken as a secondary analysis. In addition, comparisons on selected demographic and clinical characteristics will be made between “completers” and those who dropped out of treatment to help detect any biases in outcome measures. The potential effects of a number of covariates and confounders will be modelled in the major analyses (eg, borderline symptoms-MSI-BPD, medication status, drug use-modified OTI, gender, and involvement in additional mental health treatments) [72] [70].

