In a recent systematic review, Melville et al [82] found dropout rates from all Internet-based treatment programs for psychological disorders, which involved minimal therapist contact over a twenty year period, ranged from 2% to as high as 83%, with a weighted average of 31%. Interestingly, however, this weighted average was identical to that observed in face-to-face treatment for pathological gambling in the same review [82]. Therefore, assumptions that Internet-based therapies will automatically be associated with poorer adherence than face-to-face treatments appear contentious. Furthermore, the reasons for selective attrition are difficult to interpret as they may reflect the contradictory possibilities of dropout due to dissatisfaction, as opposed to dropout due to the individual feeling their needs have been met [83]. Nevertheless, attrition rates are a concern for any form of treatment and consequently the expansion of technology-based therapies demands researchers and developers consider innovative ways to engage individuals in therapy, particularly in younger populations. Feedback on the program will add to the knowledge base and aid future work in this area.

A related challenge is participant follow-up. Attempts to improve follow-up rates in the current study will include using a range of reminders, flexibility around timing of follow-up assessment (as it is Internet-based), obtaining a variety of contact details of significant others to help with locating participants, reinforcing to participants the importance of conducting follow-up, and financially compensating participants for the time required to complete the assessments ($10 vouchers for full completion of each assessment battery).

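### Missing at random is given as sufficient for both mixed models and GEE, but ordinary unweighted GEE does not in general have that property, so an outcome analysed by it can be biased if dropout follows earlier outcomes differently by arm

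*Protocol article*

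**What the plan says.** Under Data Analysis, the protocol article covers all outcome types, categorical as well as continuous, with one pair of methods: "mixed or marginal longitudinal models (ie, mixed model repeated measures, generalized estimating equation modelling) as appropriate". The next sentence begins "These approaches enable the inclusion of participants with missing data" and ends "without using inferior techniques such as last observation carried forward, when data is missing at random". Its subject is both methods, so missing at random (MAR) is offered as the sufficient condition for GEE as well as for mixed models. Weighting and imputation are not mentioned.

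Three other statements bear on the point:

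- The sample size paragraph plans for substantial loss: "A conservative dropout rate is 35% of participants at follow-up".
- Strengths and Limitations says that attrition may reflect "dropout due to dissatisfaction, as opposed to dropout due to the individual feeling their needs have been met". Both reasons are related to outcome.
- The comparison offered to detect bias sets participants who completed at least 75% of the modules against "those who dropped out of treatment to help detect any biases in outcome measures".

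Primary Outcomes defines one binary classification from the primary measures: a reliable change index of at least 1.96 together with no longer meeting the entry criterion.

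**The concern.** The two methods do not share the stated property. A likelihood-based mixed model uses each participant's observed scores to inform the missing ones and is valid under MAR if correctly specified. Unweighted GEE solves estimating equations over whatever was observed. In general it is consistent only if data are missing completely at random or if missingness depends only on covariates in the mean model. Dropout that depends on an earlier observed outcome is MAR but falls outside that condition.

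MMRM is a method for continuous outcomes, so GEE is the only method named that is made for categorical ones. The binary reliable-change outcome is therefore the likeliest to be exposed, along with any AUD outcome analysed as yes or no. What is at stake is a between-arm odds ratio that differs from 1 because of who stayed, in analyses that the article describes as protected.

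The completer comparison does not fill the gap. It concerns module use, whereas the bias depends on who answered at weeks 5, 12 and 24. A participant may complete no modules and still respond at week 24, or complete all four and not respond.

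**Working it through.** **The plan's own figures.** Inputs from Data Analysis: standardised effect 0.50, 80% power, two-sided. Alpha is not stated and is taken as 0.05. The normal approximation gives n = 2(1.960 + 0.842)²/0.50² = 62.8, so 63 per group. The noncentral t gives 64 per group with power 80.1%. Then 128/0.65 = 196.9, rounded up to 197, and 200 × 0.65 = 130 retained. The plan's 64, 128 and 200 are reproduced; nothing here changes them.

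**Set-up for the GEE claim.** From the article: visits at weeks 5, 12 and 24, 35% lost by the end, N = 200. Assumed: everyone is seen at week 5, and dropout before weeks 12 and 24 depends only on the last observed outcome (hence MAR). Y = 1 is an unfavourable result, and there is no treatment effect. Outcome-independent dropout uses a hazard of 0.194 per interval: 1 − (1 − 0.194)² = 0.35. Outcome-dependent dropout makes leaving about three times as likely after Y = 1, calibrated to the same 35%.

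**A case that can be done by hand.** Under independence GEE with separate visit-by-arm means, the week-24 estimate is simply the proportion among those observed. Take a true rate of 0.50 at each visit and a latent normal correlation of 0.6 between visits.

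- All three results equal to 1: a = 1/8 + 3·arcsin(0.6)/(4π) = 0.2786. By symmetry the same holds for all equal to 0.
- Each of the six mixed patterns: b = 1/4 + arcsin(0.6)/(2π) − a = 0.0738. Check: 2a + 6b = 1.
- Hazards 0.295 after Y = 1 and 0.098 after Y = 0 give retention s₁ = 0.705 and s₀ = 0.902.
- Observed with Y = 1 at week 24: a·s₁² + 2b·s₁s₀ + b·s₀² = 0.2924.
- Observed with Y = 0 at week 24: a·s₀² + 2b·s₁s₀ + b·s₁² = 0.3572.
- Dropout: 1 − 0.2924 − 0.3572 = 0.35, as intended.
- Apparent rate: 0.2924/0.6496 = 0.450, against a true 0.50.

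If dropout in the other arm ignores outcome, its odds are 1, and the false odds ratio is 0.2924/0.3572 = 0.82. With correlation 0.8 (hazards 0.296 and 0.099) the same formulas give a = 0.3464, b = 0.0512, and 0.2782/0.3715 = 0.75. Both agree with the simulated 0.815 and 0.746.

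**Simulation.** Bias comes from 400,000 to 600,000 subjects per arm and type I error from 2,000 to 3,000 trials of N = 200. A third structure was added: rates of 0.6, 0.5 and 0.4, with latent correlations of 0.8 between adjacent visits and 0.5 between weeks 5 and 24. Week-24 results with no true effect:

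| Dropout mechanism | Analysis | Odds ratio | Type I error |
|---|---|---|---|
| Threefold in one arm, outcome-independent in the other | Independence GEE | 0.75 to 0.82 | 8 to 13% |
| Threefold in opposite directions | Independence GEE | 0.56 to 0.67 | 21 to 36% |
| Same mechanism in both arms | Independence GEE | 1.00 | about 5% |
| Differing by arm | Exchangeable GEE, wrong structure | 1.05 to 1.09 | 5 to 8% |
| Differing by arm | Unstructured, or correct exchangeable GEE | 0.99 to 1.01 | 5 to 8% |
| All of the above | Inverse-probability-weighted GEE | 0.99 to 1.01 | about 3 to 5% |

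Part of the 5 to 8% in the fifth row is small-sample error of the sandwich variance, since about 6 to 7% also appears when both arms share one mechanism. In that shared case each arm's own rate is still biased under independence (for example 0.351 against a true 0.40), but the difference between arms is not.

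**The case against.** The strongest reply is that the statement is imprecise but the harm is hypothetical. Four parts of that reply stand.

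- A reader might infer that 35% dropout is itself enough to create a treatment difference. It is not: with one mechanism in both arms, the odds ratio is 1.00. Strengths and Limitations discusses attrition in Internet programs generally, calls its causes hard to interpret and says nothing about arms. That the mechanism differs by arm is plausible, because one arm receives active therapy and the other health information, but it is an assumption.
- A reader might quote a large false difference. One set of runs gave 11 to 14 percentage points, but it had the two arms losing opposite kinds of participant and used an independence working correlation. The article does not name one, and that choice may properly sit in the SAP. With an exchangeable working correlation the same runs gave about 0 to 4 points.
- A reader might infer that the categorical outcomes will be analysed by GEE. The wording also allows a categorical mixed model, and no between-arm model is named specifically for the reliable-change outcome.
- The plan has other safeguards: CONSORT reporting of dropout, checks of baseline and service-use differences, and covariates such as borderline symptoms, drug use and gender. GEE tolerates missingness that depends on modelled covariates. These steps narrow the gap but do not cover dependence on earlier outcomes.

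None of this rescues the sentence. It asserts a property that one of its two methods lacks in general, and nothing elsewhere in the article supplies weighting or imputation.

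**Conclusion.** The point holds as a wrongly stated property with a conditional consequence. MAR is not in general sufficient for unweighted GEE. An outcome analysed that way can show a biased arm difference if dropout depends on earlier outcomes differently in the two arms. With threefold dependence in one arm only, 35% lost per arm and independence working correlation, the size is a null odds ratio of 0.75 to 0.82 and a type I error of 8 to 13%. It shrinks to small or near zero with a well-specified working correlation.

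Only the 35%, the N of 200 and the visit times come from the article. The dropout hazards, correlations and outcome rates are assumed. The documents do not show that this trial's results will be biased. They also do not put the PHQ-9 comparison in doubt if it is analysed by MMRM. The sentence should be corrected before analysis; it is not a reason to change the design.

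**What to change.** 1. Limit the MAR statement to likelihood-based mixed models.
2. Where GEE is used, apply inverse-probability-of-dropout weights, or multiple imputation before GEE, with baseline and earlier scores in the dropout or imputation model. Alternatively, use a likelihood-based categorical mixed model and state that its effect is subject-specific, whereas GEE estimates a population-averaged one. That is a change of estimand and should be a deliberate choice.
3. Compare responders with non-responders at weeks 5, 12 and 24, by arm, on baseline and earlier scores. Add this to the module-completer comparison, which answers a separate question about adherence.

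The cost is revised wording, a little more analysis work and slightly wider intervals from weighting. The sample size stays as planned. Whether to add a sensitivity analysis for data not missing at random can be left to the SAP.

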## Results

Recruitment is currently underway with preliminary results expected in late 2014.

## Discussion

### The Present Study

The present study will assess the effectiveness of an Internet-based comorbidity intervention for young people. It is expected that depression and alcohol use outcomes for participants who complete the DEAL Project program will be significantly better than for those allocated to the control condition.

### Strengths and Limitations

A significant strength of the project is that it will be entirely Internet-based, without clinical guidance, thus, amplifying “real-world” applicability. This provides evidence on the feasibility of the intervention as a freely accessible program.

Previous trials of the SHADE program have used a guided approach [58,59], whereby therapists provide a one-session intervention at the commencement of treatment, along with 10-minute “check in” sessions at the conclusion of each computer session. This kind of approach has a number of advantages regarding therapeutic alliance, reduced dropout, improved utilization, and the ability to clarify concepts [77]. Unfortunately, such a technique is less likely to reflect real-world conditions.

A further strength of the proposed project is that the research design includes an active attention-control condition. The HealthWatch program will be used as the control, with participants being provided with a variety of health-related information. This active control [66] addresses limitations with previous clinical trials in which comparisons are allocated to a waitlist (no-treatment) control condition [78].

A potential challenge for this project will be participant dropout. Dropout rates from alcohol and other substance abuse treatment interventions are often high [79], similarly, Internet-based interventions, especially among young people, are also likely to compound these attrition rates [80]. It has been argued that a number of the strengths associated with Internet-based interventions (such as flexibility and anonymity) can quickly become weaknesses, as it may be much easier to neglect an appointment with an Internet-based program than a psychotherapist [81].

In a recent systematic review, Melville et al [82] found dropout rates from all Internet-based treatment programs for psychological disorders, which involved minimal therapist contact over a twenty year period, ranged from 2% to as high as 83%, with a weighted average of 31%. Interestingly, however, this weighted average was identical to that observed in face-to-face treatment for pathological gambling in the same review [82]. Therefore, assumptions that Internet-based therapies will automatically be associated with poorer adherence than face-to-face treatments appear contentious. Furthermore, the reasons for selective attrition are difficult to interpret as they may reflect the contradictory possibilities of dropout due to dissatisfaction, as opposed to dropout due to the individual feeling their needs have been met [83]. Nevertheless, attrition rates are a concern for any form of treatment and consequently the expansion of technology-based therapies demands researchers and developers consider innovative ways to engage individuals in therapy, particularly in younger populations. Feedback on the program will add to the knowledge base and aid future work in this area.

A related challenge is participant follow-up. Attempts to improve follow-up rates in the current study will include using a range of reminders, flexibility around timing of follow-up assessment (as it is Internet-based), obtaining a variety of contact details of significant others to help with locating participants, reinforcing to participants the importance of conducting follow-up, and financially compensating participants for the time required to complete the assessments ($10 vouchers for full completion of each assessment battery).

A final limitation is the program length. The program is considerably shorter than other interventions of this kind. However, brief interventions have been associated with significant effects for hazardous alcohol use outcomes compared to a variety of passive and active control conditions [84], especially among young populations [85]. A recent meta-analysis of 14 RCTs examined the effects of single-session personalized-feedback without therapeutic guidance on the reduction of problematic alcohol consumption in young adults [86]. The authors concluded such interventions were efficacious and cost effective and recommended the use of Internet-based approaches. This reiterated conclusions of an earlier review, which claimed that evidence supported the use of interventions that incorporated personalized feedback, either with or without practitioner support [87]. Similarly, in a systematic review of 22 RCTs of social norms-based brief interventions, Moreira et al [88] concluded that both computerized and individual face-to-face sessions appeared to reduce alcohol misuse.

Stice et al [89] reported that a four-week, group CBT-based intervention for adolescents at high-risk of depression was associated with significantly greater reductions in depressive symptoms, and a lower risk of developing depression, compared to bibliotherapy at 1- and 2-year follow-up. Scott et al [90] found primary care patients with depression who received six brief CBT sessions in combination with written educational material, recovered at significantly higher rates than those in standard care. These gains were maintained at 1-year follow-up. Similarly, a brief (4-6 sessions), solution-focused CBT treatment for depression was associated with a significantly greater reduction in symptom severity compared with standard care [91]. Brief (single session) interventions have also been found to be associated with comparable depression outcomes when compared to 10-sessions in samples with co-occurring alcohol problems [25].

Finally, in both depression and alcohol use interventions, young populations tend to be less likely to commit to the full course of sessions [92,93] and thus—especially in mild to moderate severity populations—it makes intuitive sense to adopt a brief-intervention approach.

### Conclusions

Problematic alcohol use and depression are significant problems facing young people today, however, a lack of service utilization in combination with a lack of specialized treatments mean most affected young people do not receive treatment. Internet-based interventions have the potential to overcome many of the barriers to treatment in this population. This will be the first RCT, to our knowledge, of a psychological therapy in young people with co-occurring alcohol and depressive problems [27]. The proposed trial focuses on a common clinical problem that causes substantial functional, economic, and health impacts-comorbid depression and problematic alcohol use in young people. These conditions are currently undertreated, contribute significantly to the global disease burden, and are at their peak in this age range. Offering treatments of low cost and with wide reach to affected people will address current inequities of treatment access for these problems and provide a youth-appropriate modality of treatment delivery. These results will have implications for service design and health policy, and speak to important questions about the nature of treatment effects in general. In particular, the study is in line with current national and international initiatives in eHealth and addresses important questions with both clinical and scientific significance.

## Abbreviations

AQoL: assessment of quality of life
AUD: alcohol use disorders
AUDIT: Alcohol Use Disorders Identification Test
CBT: cognitive behavior therapy
CIDI: Composite International Diagnostic Interview
CONSORT: Consolidated Standards of Reporting Trials
DASS-21: Depression Anxiety Stress Scale-21
DEAL: DEpression-ALcohol Project
MSI-BPD: McLean screening instrument for borderline personality disorder
NDARC: National Drug and Alcohol Research Centre
NHMRC: National Health and Medical Research Council
OTI: Opiate Treatment Index
PHQ-9: Patient Health Questionnaire-9
RCI: reliable change indices
RCTs: randomized controlled trials
SHADE: self help for alcohol/other drug use and depression
WHO: World Health Organization
